## Abstract

**Background:**

Article 20 of the EU Tobacco Products Directive [TPD] stipulates that e-cigarette packets and refill products must carry a nicotine addiction health warning. Although previous studies conducted in North America have found that perceived harm, addictiveness and intention to use declined following exposure to e-cigarette health warnings, possible effects of the TPD health warnings on smokers and non-smokers has not been studied. This study will investigate the effects of the EU TPD e-cigarette health warnings and a comparative harm message (COMP; developed specifically for this study) on smokers’ and non-smokers’ perceptions of harm, addictiveness and social acceptability of e-cigarettes. Additionally, the potential effects of the TPD warnings and the COMP on smokers’ intentions to purchase and use e-cigarettes will be explored.

**Methods/design:**

A sample of 2400 UK residents will be recruited in this experimental, randomised design, with Smoking status (Smoker vs. Non-smoker), TPD presence (TPD1 vs. TPD2 vs. No-TPD) and COMP presence (Presence vs. Absence) as between subjects independent variables, and Time (pre-post exposure of images) as a within subjects factor. Dependent variables comprise self-reported perceived harm, addictiveness, social acceptability, e-cigarettes’ effectiveness, intentions to purchase and use e-cigarettes. Cigarette dependence, previous e-cigarette exposure, and baseline intentions to quit will be measured as covariates.

**Discussion:**

Health warnings, such as those implemented by the TPD, may help to prevent non-smokers from e-cigarettes use, but it is possible that they may inadvertently deter smokers from initiating use and substituting their tobacco smoking for e-cigarettes use if their content is deemed too negative. It is hoped that this study will help identify the most effective message or combination of messages that encourage use among smokers without promoting use among non-smokers.

**Trial registration:**

ISRCTN registry ISRCTN76967031; date of registration: 23/10/18.

## Background

Health warnings on cigarette packets can be an effective tool to increase awareness about the dangers of smoking. Research suggests that they can act as a deterrent to smoking and promote cessation [1, 2]. Consequently, as part of a comprehensive tobacco control strategy, tobacco warning labels have become central to anti-smoking education campaigns worldwide. In addition to reducing smokers’ desire for tobacco cigarettes [3, 4], warning labels have the potential to prevent initiation in non-smokers [5]. A systematic review of 20 countries reported that strengthening health warnings on cigarette packs was associated with increased knowledge of the harms of smoking, a reduction in smoking consumption, increased quit attempts and reduced smoking prevalence [2]. Novel, larger, graphic health warnings that convey a loss-framed message (focus on harms of smoking rather than gains from quitting) and lack of branding (standardised packaging), have been shown to increase attention to the message and improve perceptions of health risks and quitting-related behaviour [6–11].

E-cigarettes are a potential tobacco harm reduction product estimated to carry approximately 5% of the health risk of tobacco smoking [12–14]. Since their introduction, uptake and awareness has increased dramatically [15, 16]. An estimated 2.9 million adults in Great Britain currently use e-cigarettes [15, 16] over half (52%) of e-cigarette users are now former smokers and 45% are continuing smokers (dual users) [16]. Smoking cessation and reduction remain the most commonly cited reasons for use [16, 17]. Though some reports suggest otherwise [18], there is increasing evidence for their effectiveness for smoking cessation [19, 20].

Although not completely risk free, growing evidence now suggests they are considerably less harmful than tobacco cigarettes [21–28]. Owing to this reduced risk profile, health and policy-makers (in the UK) consensually recommend that smokers who are unwilling or unable to quit should be encouraged to switch to e-cigarettes [12–14]. Worryingly, in recent years, public misperceptions of harm associated with e-cigarettes use have increased, with only 13% of survey respondents in the UK correctly believing that e-cigarettes are considerably less harmful than tobacco smoking [16]. In a sample of 4058 Greek residents, only 5% perceived e-cigarettes as less harmful than cigarettes in 2017 [29]. Similarly, in the US, between 2012 and 2015, the odds of perceiving e-cigarettes to be equally or more harmful than smoking has tripled [30].

The need to communicate the reduced risk status of e-cigarettes compared with tobacco cigarettes has been expressed before [31] and including relative risk messages on e-cigarette packages may be one way to communicate this. Nevertheless, current messages on e-cigarette packaging present an addiction health warning which may reinforce negative beliefs and reduce smoking cessation attempts using e-cigarettes.

Article 20 of the EU Tobacco Products Directive [TPD] [32] stipulates that e-cigarette packets and refill products must carry a health warning covering 30% of the packaging, either: i) ‘This product contains nicotine which is a highly addictive substance’, or ii) ‘This product contains nicotine which is a highly addictive substance. It is not recommended for use by non-smokers’. Aside from a recent study which suggests that addiction warnings appearing on hardware items (e.g. atomisers) lead to confusion amongst vapers [33], the impact of these health warnings on e-cigarette risk perceptions, smoking cessation and e-cigarette purchasing intentions in smokers has received very little attention. To date, research on e-cigarette health warnings has been concentrated in the US, Canada and Hong Kong. Two experimental studies have found an increase in harm and addictiveness perceptions and decrease in intention to use in US and Canadian young non-smokers following exposure to e-cigarette health warnings which conveyed the potential health and addiction risks of e-cigarettes [34, 35]. Whilst reducing e-cigarette appeal among non-smokers is clearly desirable, findings from a recent focus group with e-cigarette users and smokers suggested that health warnings that are deemed too negative may have the unintended consequence of reducing appeal among smokers who may be considering e-cigarettes for smoking cessation [31]. E-cigarette advertisements that include an addiction warning have been shown to increase health-risk beliefs in smokers and e-cigarette users, which in turn, negatively influence willingness to try the product [36]. Conversely, advertising messages that focused on differences between cigarettes and e-cigarettes (e.g. healthier, helps to quit smoking) rather than similarities (feels like smoking, relieves cravings) created more interest among smokers in trying an e-cigarette [37].

Given that comparative health messages (emphasising the reduced risk status of e-cigarettes compared with tobacco smoking) may increase the perceived utility and the value of using e-cigarettes as a quit aid (by contextualising warnings of addictiveness and the relative toxicity profile of e-cigarettes against tobacco cigarettes) they should, from an expectancy-value perspective, motivate positive health choices. Numerous approaches have suggested that *behavioural enactment* is predicated on the formation of a relevant *intention* which in turn are influenced by judgments of risk or expectancies of experiencing related outcomes (*risk perceptions*) [38, 39]. Such associations are well documented in tobacco products research. Whilst *intentions to trial* has been found to be a strong predictor of *future use* [40], other work has shown an association between *susceptibility to use* (*intentions*), *normative beliefs* (the perception that the target behaviour is socially acceptable) and *risk-based beliefs* (addiction and harm) [41]. Given this, it is likely that *exposure to advertisement materials* (i.e. health related warning labels and messages, which are likely to affect *intentions, normative* and *risk-based beliefs*) can influence *purchasing behaviours* by shaping relevant *perceptions* [42, 43]. In the current work, exposure to various warning labels will be manipulated and relevant *perceptions* measured to explore if, and to what extent, TPD warnings exert an effect on perceptions of harms, addictiveness and effectiveness of e-cigarettes and whether e-cigarettes are perceived to be socially acceptable. We will also test the effects of a comparative health message (generated prior to commencing this work and described below) alone and in conjunction with the TPD. Depending on the pilot study results, this comparative message will either convey the potential gains associated with switching away from tobacco smoking (e.g. ‘*Using an e-cigarette doubles your chances of quitting smoking’*), or will be framed to highlight gains associated with avoidance of the harmful health consequences of maintaining smoking (e.g. ‘*Completely switching to e-cigarettes lowers your risk of smoking related diseases’*).

### Objectives

This Cancer Research UK (CRUK) funded study will investigate the effects of the TPD e-cigarette health warnings and a comparative harm message on smokers’ and non-smokers’ perceptions of harm, addictiveness and social acceptability of e-cigarettes. Additional aims are to evidence the potential effects of the TPD warnings, as they are implemented, on smokers’ intentions to purchase and use e-cigarettes in future quit attempts. Lastly, the potential benefits of providing a comparative harm message either in addition to the TPD warning or as a stand-alone message will be explored.

### Hypotheses

H_1_: Participants exposed to the TPD health warning will rate e-cigarettes as more harmful and addictive compared to those exposed to i) the TPD warning combined with a comparative message (TPD+), ii) the comparative health message (COMP) alone and iii) the no message control condition.H_2_: For participants exposed to the TPD health warnings, post-exposure scores on intentions to purchase and use e-cigarettes will decrease compared to those exposed to i) the COMP alone, ii) the TPD+ messages, or iii) no message (control).H_3_: TPD health warnings will decrease quit intentions in smokers and the comparative health message (COMP and TPD+ conditions) will attenuate this effect.For H_1_ and H_2_ we will explore differences between smokers and non-smokers.

## Method

### Design

An experimental, randomised design will be used, with Smoking status (Smoker vs. Non-smoker), TPD presence (TPD1 vs. TPD2 vs. No-TPD; see below) and COMP presence (Presence vs. Absence) as between subjects independent variables, and Time (pre-post exposure of images/health messages) as a within subjects factor. Dependent variables comprise self-reported perceived harm, addictiveness, social acceptability, effectiveness, intentions to purchase and use of e-cigarettes. Smoking dependence, previous e-cigarette exposure, and baseline intentions to quit will be measured as covariates. For the E-cigarette Health Message factor, participants will be exposed to one of the six stimuli versions (see below). Messages will be displayed on e-cigarette packages as per the current EU-TPD warning labels on e-cigarette products. Warning label stimuli are:TPD1: TPD health warning as per currently implemented in the UK. “*This product contains nicotine which is a highly addictive substance*”TPD2: TPD longer health warning as currently implemented in many EU countries: “*This product contains nicotine which is a highly addictive substance. It is not recommended for non-smokers*”COMP: Comparative health message as generated in the pilot study (using the same parameters used for the TPD warning labels; font, font colour, size and placement on the pack)TPD1+: The TPD health warning (TPD1) in combination with the comparative message (using the same parameters above)TPD2+: The TPD longer health warning (TPD2) in combination with the comparative message (using the same parameters as above).No message: A no message condition using the same e-cigarette packages

The primary outcome variables for this study will be smokers’ and non-smokers’ perceptions of e-cigarettes associated with i) harm, ii) addictiveness, iii) social acceptability, iv) effectiveness, v) intentions to purchase, and vi) intentions to use e-cigarettes. Key outcome variables specifically for smokers will be intentions (i) to quit and (ii) use e-cigarettes in a quit attempt. All measures will be taken before and after exposure to messages.

### Study population/ sample size

The sample will include 2400 participants (*N* = 1200 smokers; N = 1200 non-smokers) all residents in the UK. Given an effect size of between OR = 0.41 and 0.52 (the effect sizes observed in intent to purchase e-cigarettes between control, ingredient and industry warnings respectively) [44] and converting the OR to effect size F using Chinn [45] methodology (Fs = 0.41–0.52) suggest the current study design will need to be powered to detect medium to large effects. The proposed sample (*N* = 1200) allows for detection of small (F = 0.12) main effects and interactions.

Smokers will be matched to the target population of smokers’ demographics in the general population using ONS data by deriving best estimates of required numbers in each condition required at levels of age (banded into two segments), gender (two segments) and Socio-Economic Status (SES) (four segments). The latter will be derived from the number of participants required in the four SES segments (managerial and professional occupations; intermediate occupations; routine and manual occupations; never worked or unemployed). Thereafter, the number in each of these bands for gender and then age bands will be derived resulting in a target number of each of the 16 combinations. A panel agency (Market Research Focus Group Recruiter (MRFGR, a division of AGENTC Ltd)) will be contracted to recruit and randomise to each of these targets using a set of block lists provided by the research team. The same stratification levels will be used for non-smokers matched to population level statistics.

Block randomisation will be used for allocation of conditions and demographic variables (including smoking status) will be stratified so that the sample of smokers is representative of the target population in line with ONS data. Each participant will be assigned to one of the six conditions to obtain equal group sizes using IBM SPSS.

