### Statistical analysis

Firstly, a series of ANCOVAs will be used to test for differences between TPD1 and TPD2 scores on Time 2 perceived ratings of e-cigarette i) harm, ii) addictiveness, iii) social acceptability, iv) effectiveness, v) intentions to purchase and vi) intention to use. We will control for Time 1 measurements of the dependent variable (DV) in each analysis (thus testing differences between TPD1 and TPD2 conditions, controlling for baseline differences).

If no differences between TPD1 and TPD2 are observed, we will collapse these two conditions. The subsequent analysis will use a series of ANCOVAs with 3 between-factors Smoking status (Smoker vs. non-smoker), TPD presence (Present vs. Absent), COMP presence (Present vs. Absent). Dependent variables (DV) will consist of Time 2 perceived ratings of e-cigarette i) harm, ii) addictiveness, iii) social acceptability, iv) effectiveness, v) intention to quit, vi) intention to purchase and vii) intention to use e-cigarettes. We will control for Time 1 measurements of the DV in each analysis (thus testing for change over time, controlling for baseline differences). All main and interactive simple effects will be tested, and we also specifically plan a-priori comparisons between the TPD/no COMP conditions against i) no TPD/no COMP, ii) TPD/COMP, iii) no TPD/COMP, and COMP alone with i) no TPD/no COMP, ii) TPD + COMP, iii) TPD/no COMP. These will be conducted at each level of smoking status.

In addition, the same ANCOVAs will be repeated with the same IVs, DVs and covariates, but additionally controlling for cigarette dependence, previous e-cigarette exposure, and baseline intentions to quit. If differences between TPD1 and TPD2 are observed, we will conduct the above analyses, with TPD presence being expanded to have 3 levels (TPD1 vs. TPD2 vs. No-TPD). The a-priori comparisons will be conducted twice as described above, once with TPD being replaced by TPD1 and the second time with TPD being replaced by TPD2.

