Exploratory analyses will be run on each of the variables to check for data distribution, outliers and the type of analysis required. Outliers will be considered on a case-by-case basis and discarded after verification. Analyses will be run using ‘Exclude cases pairwise’ so cases with missing data will not be included in the analysis. Demographics (age, occupation and highest qualification) may be related to perceptions of e-cigarettes as well as intentions to purchase and use e-cigarettes, and quit intentions, so we will explore the relationships between demographic variables and the aforementioned outcome variables.

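### Conditions are allocated within age, gender and SES cells, but the ANCOVAs leave these factors out, so the reported standard errors may be slightly too large

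*Protocol article*

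**What the plan says.** **Allocation** (protocol article, *Study population/ sample size*). The team derives "required numbers in each condition required at levels of age (banded into two segments), gender (two segments) and Socio-Economic Status (SES) (four segments"), giving 16 combinations. The panel agency is to "recruit and randomise to each of these targets using a set of block lists provided by the research team". For the other smoking group, "The same stratification levels will be used for non-smokers matched to population level statistics". The summary sentence is that "Block randomisation will be used for allocation of conditions and demographic variables (including smoking status) will be stratified"; it goes on to give representativeness against ONS data as the purpose. Finally, "Each participant will be assigned to one of the six conditions to obtain equal group sizes using IBM SPSS". The sample is 1200 smokers and 1200 non-smokers.

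**Analysis** (*Statistical analysis*). The first-step comparison of TPD1 with TPD2 names only the Time 1 score as a control. The main ANCOVAs have smoking status, TPD presence and COMP presence as factors, and "We will control for Time 1 measurements of the DV in each analysis". A repeat adds cigarette dependence, previous e-cigarette exposure and baseline intentions to quit. Age, gender and SES are in none of these models. The same section says that age, occupation and highest qualification may be related to the outcomes, and that "we will explore the relationships between demographic variables and the aforementioned outcome variables".

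**The concern.** When the six conditions are balanced within cells, differences between cells cannot contribute to a difference between conditions. If the model omits the cells, that between-cell variance nevertheless stays in the error term. The standard error then describes a less well balanced trial than the one that was run, so intervals are too wide and tests conservative.

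The plan is also uneven: it models one stratification factor, smoking status, and leaves out the other three, although it expects two of them (age and occupation, its measure of SES) to be possibly related to the outcomes.

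What is at stake is limited to reported precision. It bears most on the planned comparisons made within each smoking group, where a single condition has about 1200/6 = 200 people. It also tilts the decision to collapse TPD1 and TPD2 very slightly towards collapsing, because that decision rests on no difference being observed.

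**Working it through.** **The plan's own figure.** The article gives no variance figure for the strata. Its only precision statement is that N = 1200 can detect F = 0.12, with alpha, power and numerator degrees of freedom not given. With an assumed two-sided alpha of 0.05, one covariate and noncentrality f²N = 0.12² × 1200 = 17.28, power is 98.6%, 96.9%, 91.4% and 81.0% for 1, 2, 5 and 11 numerator df. The figure is plausible but cannot be reproduced exactly, and it does not settle this point.

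**Inputs from the article.** 2 age bands × 2 genders × 4 SES groups = 16 cells per smoking group, hence 32 strata; six equal conditions, hence about 200 per condition in each smoking group.

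**Assumed input.** R², the share of the outcome variance left after Time 1 adjustment that the strata explain. Range 0 to 0.10, with 0.01 to 0.05 as the working range.

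**Formulas.** With balance within strata:

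- Reported SE ÷ stratum-adjusted SE = 1/√(1 − R²)
- True type I error of the unadjusted test = 2 × [1 − Φ(1.96/√(1 − R²))]
- Power of the unadjusted test, where the adjusted test has 80% = Φ(1.96 + 0.842 − 1.96/√(1 − R²))

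| Assumed R² | SE overstated by | Type I error | Power |
|---|---|---|---|
| 0 | 0% | 0.050 | 80.0% |
| 0.01 | 0.5% | 0.049 | 79.7% |
| 0.02 | 1.0% | 0.048 | 79.4% |
| 0.05 | 2.6% | 0.044 | 78.5% |
| 0.10 | 5.4% | 0.039 | 76.9% |

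For example, at R² = 0.05: 1/√0.95 = 1.026, and 1.96 × 1.026 = 2.011, which gives a two-sided error of 0.044.

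**Simulation check.** One smoking group of 1200, 16 cells of nearly equal size, blocks of six, an assumed Time 1/Time 2 correlation of 0.7, and 3000 runs per setting. The contrast is collapsed TPD alone (400) against no message (200).

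- Expected unadjusted SE: √(1 − 0.7²) × √(1/400 + 1/200) = 0.714 × 0.0866 = 0.0618. Simulated: 0.0619.
- At R² = 0.05, expected adjusted SE: 0.0618 × √0.95 = 0.0603. Simulated: 0.0603.
- At R² = 0.05, the empirical SD of the estimate was 0.0591 both with and without the strata in the model. So omitting them affects the reported SE, not the estimate.
- At R² = 0.05, simulated type I error was 0.043 unadjusted and 0.048 adjusted.
- At R² = 0, both models gave an SE of 0.0619, so adjusting for strata that explain nothing cost nothing visible.

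Monte Carlo error on a rejection rate of 0.05 is √(0.05 × 0.95/3000) = 0.004. The type I error figures therefore rest on the formula; the simulation confirms the SE ratio and the unchanged estimate.

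**Degrees of freedom.** Main effects: 1 (age) + 1 (gender) + 3 (SES) = 5. All strata: 32 − 1 = 31, less 1 for smoking status already in the model = 30. The collapsed main ANCOVA has 2400 − 8 − 1 = 2391 residual df, leaving 2386 or 2361.

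**The case against.** The strongest objection is that this hardly matters. The Time 1 score is the same item rated in the same session, before a 30-second exposure, and smoking status is already a factor in the main models. Together they may absorb most of any demographic effect, so the residual R² could be close to zero. This stands: the 0.01 to 0.05 range is an assumption, and zero is plausible.

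It can also be said that the cells are ONS-matched quotas meant for representativeness rather than a device for precision. That is the stated purpose. But target numbers per condition and block lists within the cells balance the conditions across them, whatever the motive.

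A third objection is that a condensed article may leave adjustment for design strata to an analysis plan that is not shown. This carries less weight here, because the article itself lists the model terms and gives a second explicit covariate list, and neither contains these factors.

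Three stronger readings are tempting and should be resisted:

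- A reader might infer that the precision gained by stratifying is lost, and convert an R² of 0.01 to 0.05 into 24 to 120 of the 2400 participants. The estimate keeps that precision; only its reported SE fails to credit it.
- A reader might infer bias or an inflated false-positive rate. Neither follows: the tests err on the conservative side.
- A reader might infer that covariates will be picked after looking at their relation to the outcomes. The article plans to explore those associations but nowhere says that the models will be chosen or refitted from them. Its covariates are named in advance.

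**Conclusion.** The point holds as a minor one. Conditions are allocated within age, gender and SES cells, and the listed ANCOVAs omit those factors. The effect estimates are unbiased and as precise as the design makes them, but reported SEs are too large whenever the strata predict the outcome beyond Time 1: about 0.5% at a residual R² of 0.01 and 2.6% at 0.05, with a power cost of about 0.3 to 1.5 percentage points from 80%. If R² is 0, there is no effect.

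These figures rest on the assumed R², on alpha 0.05, and on allocation that is in fact balanced within cells. Cells set from ONS proportions will be unequal, and sparse ones may leave blocks incomplete; the simulation, with nearly equal cells, does not cover that.

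**What to change.** In *Statistical analysis*, add one sentence: every ANCOVA, including the first-step TPD1 against TPD2 comparison and the repeat with additional covariates, will include age band, gender and SES as fixed covariates alongside the Time 1 score, banded as in the block lists.

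Main effects cost 5 df. Adjusting for all 32 strata costs up to 30 df beyond smoking status, which is also affordable at this sample size, although sparse cells make main effects the simpler choice. No new data are needed, since age, gender and four-category occupation are already collected.

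The exploratory analysis of demographics can stay as it is, because the plan does not use it to choose covariates.
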